### **Study Design**

**The scientific integrity of the study and the credibility of the study data depend substantially on the study design and methodology. The design of the study should include information on the type of study, the research population or the sampling frame, and who can take part (e.g. inclusion and exclusion criteria, withdrawal criteria etc.), and the expected duration of the study**

**(The same study can be described in several ways, and as complete a description of the study as possible should be provided. For example, a study may be described as being a basic science research, epidemiologic or social science research, it may also be described as observational or interventional; if observational, it may be either descriptive**

**or analytic, if analytic it could either be cross-sectional or longitudinal etc. If experimental, it may be described as a controlled or a non controlled study. The link below provides more information on how to describe a research study**

The human controlled intervention study is conducted according to the guidelines laid down in the declaration of Helsinki, and was approved by the Ethical Committee of the Ghent University Hospital (B670201630414). Participants, members of the research group and familiars, are contacted providing an invitation letter and can register for the study within two weeks after the call. All participants have to sign an informed consent. Each participant is informed on his/her right to withdraw from the study at any time and to consult a doctor immediately and inform us if they fell not right during the study but no adverse event are reported for any volunteers. Besides, no medical examinations or interventions are carried out in this study. The study is performed with 20 volunteers throughout an intervention and longitudinal trail, and recruited in Flanders (Belgium). All people older than 18 years old can take part in the study, less pregnant or breast-feeding women due to the potential risk to both mother and foetuses and persons with severe problems with liver, bile or kidney due to related risks for interferences with the mycotoxin metabolism. The volunteers are instructed to file a socio-demographic questionnaire involving details on age, gender, length, body weight, smoking, diseases, drugs or supplements, pregnancy, breast-feeding, diet and daily coffee consumption.

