The subjects have to follow a strict cereal-free diet during 3 days (Figure 1). Cereal-based foods and foods containing possible traces of wheat, rye, oats, maize and rice are restricted (*i.e.* bread and bread-based products, breakfast cereals, oat meal, muesli, cereal bars, waffles, cakes, (un)pealed rice, polenta, pizza, tortilla, pasta, popcorn, cereal-based chips, maize, beer, wine, pan meal and sauce-binders). The subjects are asked to detail their daily food intake through a questionnaire. On the third day in the morning, the subjects receive an oral bolus of DON or DON-3-glucoside based on the TDI ( $1\text{ }\mu\text{g/kg}$  body weight) and their body weight. The volunteers did the study twice: 1) DON administration and 2) DON-3-glucoside administration, between the two mycotoxin administration there are a washout period of two months. In addition, a control group of 4 volunteers follow the same protocol, however do not receive a bolus of DON or DON-3-glucoside after the cereal-free diet.

At day 3, volunteers have to collect a urine sample before the administration of the DON or DON-3-glucoside bolus (Figure 1). From the moment of administration, the 24-hours urine sample collection is requested. We deliver to each volunteer 12 containers (1L) to collect the urine. For every sampling point, time (hour of urine collection) and voided volume is recorded. All samples will be individually aliquotted to 20 mL, and stored in the freezer at  $-20^{\circ}\text{C}$  upon analysis. The samples are analysed with a Waters Acquity UPLC system coupled to a Quattro XEVO TQS mass spectrometer (Waters, Manchester, UK) was used to analyse the urine samples. Data acquisition and processing is performed with MassLynx™ version 4.1 and

QuanLynx® version 4.1 software (Waters, Manchester, UK). A Waters Acquity UPLC® HSS T3 (2.1 x 100 mm, 1.8 µm) column is applied (Waters, Manchester, UK).

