The results are submitted an statistical analysis. Firstly, all obtained results are carried out on molar basis taking the molecular weight of the analytes (DON, 296 g/mole; DON-3-glucoside, 458 g/mole; DON-3-glucuronide and DON-15-glucuronide, 472 g/mole; DOM-1, 280 g/mole; 3-ADON and 15-ADON, 338 g/mole) and the total volume of each sampling point into account. Associations between independent and dependent variables are assessed by using univariate and multivariable linear regression models. Independent variables included age (years), gender, body mass index (BMI), and the consumption of coffee. The statistical analysis was performed using the software Microsoft Excel® 2010 and SPSS® 15.0.

**Figure 1.** Scheme of the study design.

[figure not shown]

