Volunteers have to be three days without eating cereals. It is difficult to control their diet for 24 h, so we absolutely trust in their free cereals diet. However, we know that if some volunteers do not follow the diet we will detect DON levels in the “blank” urine (the urine before toxin administration) and they have to repeat the intervention study. So, although we do not control totally the volunteers diet we have the “blank” urine as control of their good diet following. We deliver a list with the allowed and not allowed food to clarify even more the restricted food to the volunteers (Figure 2). On the other hand, we add four volunteers which will not take toxin administration but they do not know they are not taking the toxin administration just water. The 4 control volunteers will provide us information to compare the results. The control volunteers are random selected from the 20 volunteers. 2 males and 2 females will be randomly selected for control.

The volunteers have to answer a questionnaire where we ask for factors that could affect the toxin excretion (Figure 3). Moreover, we ask again about pregnant or breast feeding people as well as

kidney, liver or bile problems to be sure again that pregnant or breast feeding women and people with kidney, liver or bile problems are not included in the study.

Stickers with the code for each sample will be delivered to the volunteers with the urine collection containers. The volunteers have to stick each code to the urine sample and they have to add the hour of urine collection for each sample. This process is explained in detail to each volunteer when they come to collect the containers, moreover, we supply a completely detailed procedure about how to take the samples, where we added a phone number contact to call in case of doubts during the study.

Once, we received the samples from each volunteer we introduced the code, the hour and the volume for each sample in excel file and we take two aliquots of 20 mL for each samples and we stored until analysis in the freezer at -20 °C.

Then, the samples are analysed by LC-MS/MS with a previously validated method.

A flow diagram with timing assessments has been made with the study design and procedures (Figure 4).

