### **Data Management and Statistical Analysis**

**The protocol should provide information on how the data will be managed, including data handling and coding for computer analysis, monitoring and verification. The statistical methods proposed to be used for the analysis of data should be clearly outlined, including reasons for the sample size selected, power of the study, level of significance to be used, procedures for accounting for any missing or spurious data etc. For projects involving qualitative approaches, specify in sufficient detail how the data will be analysed.**

Firstly, we agree a coding system for the samples. The coding system is that all samples have two number separated by a "." where the first number is the volunteer id and the second number is the number of the sample of each volunteer. So the first urine sample of the volunteer 1 is 1.1 and the second sample of the volunteer 1 was 1.2. On the other hand, the second sample for the volunteer 2 is 2.1 and the second samples of the volunteer 2 is 2.2. We introduce an excel file all the information for each volunteer id.

Once we analyse the samples, the data of each sample is introduced in the same excel file and the results of each mycotoxin are introduced separately. Then, all obtained results are carried out on molar basis taking the molecular weight of the analytes (DON, 296 g/mole; DON-3-glucoside, 458 g/mole; DON-3-glucuronide and DON-15-glucuronide, 472 g/mole; DOM-1, 280 g/mole; 3-ADON and 15-ADON, 338 g/mole) and the total volume of each sampling point into account. Associations between independent and dependent variables are assessed by using univariate and multivariable linear regression models. Independent variables include age (years), gender, body mass index (BMI),

and the consumption of coffee. The statistical analysis is performed using the software Microsoft Excel® 2010 and SPSS® 15.0.

The excretion profiles are based in values obtained each hour after the bolus administration from a varying number of volunteers per time period. For instance, results from 61 to 120 minutes are clustered in the second hour.

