### **Quality Assurance**

**The protocol should describe the quality control and quality assurance system for the conduct of the study, including GCP, follow up by clinical monitors, DSMB, data management etc.**

The human controlled intervention study is conducted according to the guidelines laid down in the declaration of Helsinki. The standard administration is prepared with commercial standard and the commercial company provided us the quality certification. Moreover, several toxin analysis in the bolus administration are performed before the toxin administration.

Internal standard is used in all the samples. The internal standard offers a correction for the loss of analyte during sample preparation. Moreover, a calibration curve is made for every 40 samples to correct possible variations among different analysis days.

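### DON is given first and DON-3-glucoside second with no randomised order, so any difference between them is fully confounded with period

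*Protocol*

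**What the plan says.** The Study Design section, repeated in the Project summary, numbers the two administrations: "The volunteers did the study twice: 1) DON administration and 2) DON-3-glucoside administration". On timing it adds that "between the two mycotoxin administration there are a washout period of two months". Neither section says that the order is randomised or varies between volunteers.

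The only random allocation in the protocol is in the Methodology section: "The control volunteers are random selected from the 20 volunteers". The Study Design section instead introduces them as extra: "In addition, a control group of 4 volunteers follow the same protocol". The controls receive water.

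On analysis, the Data Management and Statistical Analysis section says: "Associations between independent and dependent variables are assessed by using univariate and multivariable linear regression models". The independent variables listed are age, gender, BMI and coffee consumption. The section does not say whether the two occasions enter one regression or separate ones, or whether the dependent variable is per void, per hour or per 24 hours.

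On the assay, the Quality Assurance section says that an internal standard is used in all samples and that "a calibration curve is made for every 40 samples to correct possible variations among different analysis days". No run order is given.

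**The concern.** Every dosed volunteer appears to receive DON on the first occasion and DON-3-glucoside on the second, two months later. Anything else that changes between the occasions then travels with the toxin. Several such changes are plausible. The season moves on. Volunteers have already followed the diet once, and the Methodology section admits that the diet is largely taken on trust. They have also already practised a self-administered 24-hour urine collection, where missed voids would lower apparent recovery. Assay conditions may differ too: the Duration of the Project section has analysis running from April to July while collection ran from March to June.

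At stake is how the two excretion profiles are read against each other. The rationale asks how far the glucoside adds to DON exposure, and the expected outcomes cover the toxicokinetics of both compounds. Readers will compare recovery and speed of excretion between the two, and nothing in the protocol warns that a difference may reflect the occasion.

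**Working it through.** The protocol states no sample-size, power or significance calculation, so there is no figure to reproduce. The check is whether the design can separate toxin from period.

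**Inputs**
- Two occasions per dosed volunteer, DON then DON-3-glucoside (Study Design; Project summary).
- 20 volunteers: "The study is performed with 20 volunteers throughout an intervention and longitudinal trail". If the 4 controls come out of the 20, then 20 − 4 = 16 are dosed; if they are additional, 20 are dosed. Both are used.
- Four volunteer-level covariates (Data Management and Statistical Analysis).
- Not given, so assumed: two-sided 5% level and within-volunteer correlation from 0.3 to 0.9. The size of any period effect is not given and is left as a symbol.

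**Step 1: order as written.** For volunteer i on occasion j, let y = v_i + π_j + τ_toxin + error. The within-volunteer difference, second minus first, has expectation

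(τ_glucoside − τ_DON) + (π_2 − π_1).

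The period change enters one for one, and averaging over more volunteers does not remove it. In matrix terms, the model has n volunteer columns, 1 period column and 1 toxin column:
- n = 16: 16 + 1 + 1 = 18 columns, rank 17.
- n = 20: 20 + 1 + 1 = 22 columns, rank 21.

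The toxin and period columns are identical (correlation 1.0). This model already contains toxin, period and volunteer terms, so adding them to the regression would not help. The cause is the order.

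**Step 2: counterbalanced order.** Write π = π_2 − π_1 and τ = τ_glucoside − τ_DON. The mean second-minus-first difference is π + τ for those taking DON first and π − τ for those taking the glucoside first. Half the difference between the two means is [(π + τ) − (π − τ)]/2 = τ. The design becomes full rank (18 of 18; 22 of 22) and the toxin–period correlation is 0, assuming no carry-over.

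**Step 3: do other features rescue the fixed order?**
- The two-month washout deals with carry-over, that is, residue of the first dose. It does nothing about a change in conditions.
- The controls receive no toxin, so they can show a change in background levels but not a change in the recovery of an administered dose.

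**Step 4: the covariate regressions, a separate and conditional matter.** If both occasions were pooled as independent records, the variance of a volunteer-level coefficient would be understated by a factor of about 1 + ρ. At ρ = 0.5 the standard-error factor is √1.5 = 1.22, and a large-sample approximation gives a type I error of 2 × [1 − Φ(1.96/1.22)], about 11%. Simulation with four covariates (10,000 runs per setting) gives somewhat more:

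| Assumed ρ | Pooled, n = 16 | Pooled, n = 20 |
|---|---|---|
| 0.3 | 10.0% | 8.8% |
| 0.5 | 12.9% | 12.0% |
| 0.7 | 16.3% | 15.7% |
| 0.9 | 19.7% | 18.5% |

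With one model per toxin and one value per volunteer, the simulated type I error was 4.7% to 5.5%, so there is no inflation.

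**The case against.** The strongest reply is that no toxin comparison is planned. The Study goals and objectives section aims to describe excretion patterns and rates, and each profile, including which metabolites appear after DON-3-glucoside, can be described without a between-toxin test. This stands, and it limits the point to an implied comparison. It does not remove it, because the same people receive both compounds and the stated purpose invites setting the profiles side by side.

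The numbering might also be a list and not a sequence, and the two design figures are not available here. That is possible, but no text gives another order. If the order varied, one sentence would settle it.

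The period effects named may also be small. Pre-dose urine with repetition after a diet failure limits diet drift, and the internal standard and recalibration are safeguards. Samples are frozen, and nothing shows that assay batch follows occasion, so batch is only a possible contributor. All of this bears on the size of the bias, not on whether toxin and period can be separated.

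A reader might go further and infer that the regression treats repeat records as independent, or that its missing toxin, period and volunteer terms cause the confounding. The document supports neither. Pooling is never stated, separate per-toxin models fit the text, and the confounding would remain with those terms included. Model detail of this kind may also properly sit in an analysis plan that is not shown.

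**Conclusion.** The point holds for the order of administration. As written, any difference between DON and DON-3-glucoside in excretion is fully confounded with period, whether 16 or 20 volunteers are dosed. This rests on reading the numbered administrations as a sequence, which is the only order the text gives.

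Complete confounding is not the same as large bias. The bias equals the period change in recovery, for which the document offers no figure, so its size and direction are unknown. It affects the comparison between toxins. It does not stop each profile from being described for the occasion on which it was observed.

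The type I error of about 12–13% at an assumed correlation of 0.5 with four covariates applies only if the two occasions are pooled as independent. It is not a demonstrated fault of the plan.

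**What to change.** **For any volunteers not yet dosed:** randomise half to each order, balanced by gender, and include period in the toxin comparison. The cost is a short allocation list, with the small downside that both boluses must be ready at the start.

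**If dosing is complete:** the Duration of the Project section reports collection and assay as finished and the data as under analysis, so this is the likely case. Three changes of wording are then enough.
1. Compare the toxins within volunteer. At an assumed correlation of 0.5 the standard error is √(1 − 0.5) = 0.71 of that from an unpaired comparison. Pairing improves precision but does not remove the confounding.
2. State that the covariate regressions are fitted per toxin with one value per volunteer, or with a random volunteer effect if the occasions are pooled.
3. State in the protocol and the report that all volunteers took DON first, and that toxin and period effects cannot be separated.

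These cost a few sentences and no new data. If the order did in fact vary, state how it was assigned and record it for each volunteer.

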## **Methodology**

The methodology section is the most important part of the protocol. It should include detailed information on the interventions to be made, procedures to be used, measurements to be taken, observations to be made, laboratory investigations to be done etc. If multiple sites are engaged in a specified protocol, methodology should be standardized and clearly defined.

Interventions should be described in detail, including a description of the drug/device/vaccine that is being tested. Interventions could also be in the realm of social sciences for example providing training or information to groups of individuals.

Procedures could be biomedical (collection of blood or sputum samples to develop a diagnostic test), or in the realm of social sciences (doing a questionnaire survey, carrying out a focus group discussion as part of formative research, observation of the participant's environment, etc.).

Standardized and/or documented procedures/techniques should be described and bibliographic references, if not provided earlier should be provided. Instruments which are to be used to collect information (questionnaires, FGD guides, observation recording form, case report forms etc.) must also be provided.

In the case of a randomized controlled trial additional information on the process of randomization and blinding, description of stopping rules for individuals, for part of the study or entire study, the procedures and conditions for breaking the codes etc. should also be described.

A graphic outline of the study design and procedures using a flow diagram must be provided. This should include the timing of assessments.

Volunteers have to be three days without eating cereals. It is difficult to control their diet for 24 h, so we absolutely trust in their free cereals diet. However, we know that if some volunteers do not follow the diet we will detect DON levels in the “blank” urine (the urine before toxin administration) and they have to repeat the intervention study. So, although we do not control totally the volunteers diet we have the “blank” urine as control of their good diet following. We deliver a list with the allowed and not allowed food to clarify even more the restricted food to the volunteers (Figure 2). On the other hand, we add four volunteers which will not take toxin administration but they do not know they are not taking the toxin administration just water. The 4 control volunteers will provide us information to compare the results. The control volunteers are random selected from the 20 volunteers. 2 males and 2 females will be randomly selected for control.

The volunteers have to answer a questionnaire where we ask for factors that could affect the toxin excretion (Figure 3). Moreover, we ask again about pregnant or breast feeding people as well as

kidney, liver or bile problems to be sure again that pregnant or breast feeding women and people with kidney, liver or bile problems are not included in the study.

Stickers with the code for each sample will be delivered to the volunteers with the urine collection containers. The volunteers have to stick each code to the urine sample and they have to add the hour of urine collection for each sample. This process is explained in detail to each volunteer when they come to collect the containers, moreover, we supply a completely detailed procedure about how to take the samples, where we added a phone number contact to call in case of doubts during the study.

Once, we received the samples from each volunteer we introduced the code, the hour and the volume for each sample in excel file and we take two aliquots of 20 mL for each samples and we stored until analysis in the freezer at -20 °C.

Then, the samples are analysed by LC-MS/MS with a previously validated method.

A flow diagram with timing assessments has been made with the study design and procedures (Figure 4).

Figure 2. List with the allowed and not allowed food during the intervention diet. The list is delivered to the volunteers to be better informed about the diet to follow during the study. Moreover, we added some diet recommendations to be followed during the days of restriction diet.

| Restricted food                                                                                                                                                                                                        | Permitted food                                                                                                                                                           |
|------------------------------------------------------------------------------------------------------------------------------------------------------------------------------------------------------------------------|--------------------------------------------------------------------------------------------------------------------------------------------------------------------------|
| 
 
• Pasta
 
• Breads or similar (small toasts, sliced bread...)
 
• Baking products (cookies, muffins...)
 
• Breakfast cereals
 
• Snacks
 
 | 
 
• Fruit
 
• Vegetable
 
• Meat
 
• Fish
 
• Nuts
 
• Dairy products
 
• Eggs
 
 |
| Beverages                                                                                                                                                                                                              |                                                                                                                                                                          |
| 
 
• Beer
 
                                                                                                                                                               | 
 
• Other
 
                                                                                                                |

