Furthermore, free mycotoxins, like DON, might not be the only hazard for consumer's health, because the so-called modified mycotoxins are also widely common in food. Modified mycotoxins are toxins attached to more polar functional groups, such as glycosyl residues or sulfates, or to polymeric carbohydrates or protein matrices (Berthiller, Schuhmacher, Adam, & Krska, 2009; Rychlik, et al., 2014). The modified mycotoxins may have plant, fungal, mammalian and food processing origins. A major concern and potential risk for consumers is the possible hydrolysis of modified mycotoxins into their toxic free forms during mammalian digestion (Broekaert, et al., 2015; Grabley, Gareis, Bockers, & Thiem, 1992; V. Nagl, et al., 2014). Contrary to the wealth of information on the free mycotoxins, only limited data are available for mycotoxin derivatives in foods. The co-occurrence of free and modified DON forms has been documented in raw wheat, especially with focus on deoxynivalenol-3-glucoside (DON-3-glucoside), 3-acetyldeoxynivalenol (3-ADON) and 15-acetyldeoxynivalenol (15-ADON). Reported levels of DON-3-glucoside are variable, however, the concentration of DON-3-glucoside can be high and even the same as DON in processed cereals ([name], et al., 2012). 3-ADON and 15-ADON have also been detected in cereals and cereals products with a lower incidence than DON-3-glucoside ([name], et al., 2012). (Berthiller, et al., 2011) demonstrated that several lactic acid bacteria hydrolyse DON-3-glucoside in vitro, which has been a first step to prove the toxicological relevance of DON-3-glucoside. On the other hand, 3-ADON and 15-ADON are rapidly converted to DON during digestion (Broekaert, et al., 2015; Versilovskis, et al., 2012). Thus, due to the high presence of DON conjugates in food and the easy transformation of them to DON, the FAO/WHO Expert Committee (JEFCA) considered DON-3-glucoside to be an additional contributing factor to total dietary exposure to DON (JECFA, 2010).

To know the DON exposition, analysis of urinary levels of DON has been proposed due to its short excretion half-life. However, different studies showed that DON glucuronides, which are the main phase II metabolites of DON, are the most common DON form in urine, specially DON-

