3-glucuronide and DON-15-glucuronide (Warth, et al., 2012). So, the analysis of glucuronides forms in urine is crucial for the study of trichothecenes biomarkers, because about 90 % of DON excreted via urine is conjugated with glucuronic acid. For the glucuronides determination, a preliminary approach was developed based on the breakage of deoxynivalenol-glucuronides and subsequent determination of “total deoxynivalenol” (sum of free and released mycotoxins by hydrolysis). Afterwards, a direct method for quantification of glucuronides such as deoxynivalenol-3-glucuronide and deoxynivalenol-15-glucuronide was developed. The analytical developments permitted to find strong correlations between the sum of urinary deoxynivalenol and its glucuronidated metabolites (Turner, White, et al., 2010; Warth, Sulyok, Berthiller, Schuhmacher, & Krska, 2013). These investigations revealed the power of biomarker driven work when compared to traditional exposure assessment by analyzing food stuff. However, the analysis of DON in urine presents some uncertainties and limitation to fully validate the DON excretion metabolism and renal excretion. Firstly, biomonitoring data may depend on the moment in time when the sample is collected (Clewell, Tan, Campbell, & Andersen, 2008). Furthermore, there is a lack of information in the absorption and excretion rate of it. Finally, the high presence of DON conjugates in food like DON-3-glucoside or acetyl-deoxynivalenol (ADONs) add more uncertainties for the correlation between urinary DON and DON intake.

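### The pre-dose blank, offered as the control of diet adherence, cannot show a cereal lapse during the 24-hour collection, and the analytes that make it positive are not stated

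*Protocol*

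**What the plan says.** Under Study Design, "The subjects have to follow a strict cereal-free diet during 3 days", and the bolus is given on the morning of the third day. On sampling: "At day 3, volunteers have to collect a urine sample before the administration of the DON or DON-3-glucoside bolus". Then: "From the moment of administration, the 24-hours urine sample collection is requested". The instructions to volunteers give 7:00 on day 3 to 7:00 on day 4 as an example.

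The Methodology section says of adherence: "we know that if some volunteers do not follow the diet we will detect DON levels in the" blank urine, in which case the volunteer repeats the study. It adds that "although we do not control totally the volunteers diet we have the" blank as the control of adherence.

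Three other provisions bear on diet:
- a daily food questionnaire (Study Design);
- a restart when a volunteer is aware of a dietary mistake (Problems Anticipated);
- four undosed controls used for comparison (Methodology).

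The Rationale states that "about 90 % of DON excreted via urine is conjugated with glucuronic acid". The statistical section lists DON, DON-3-glucoside, both DON glucuronides, DOM-1 and two acetylated forms among the analytes, all put on a molar basis.

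**The concern.** The outcome is what appears in urine during the 24 hours after the bolus. The protocol describes no label that would separate administered from dietary DON, so cereal eaten in that window is counted as excreted bolus. In that volunteer, recovery is biased upward and the excretion profile can show a late rise that has nothing to do with the dose. In the DON-3-glucoside period, dietary DON could be read as hydrolysed glucoside, which is a central question of the study.

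The check that the protocol trusts is completed before this window opens. It is also stated as a certainty, while the criterion for a positive blank is left undefined.

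**Working it through.** **Timing.** If the diet days are days 1 to 3 and the blank is passed on the morning of day 3, about 48 of the 72 diet hours precede it and about 24 follow it (24/72 = 33%). Those last 24 hours are the whole outcome window. A lapse after the blank cannot appear in it, whichever analytes are read and however sensitive the assay.

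**What else covers the window in a dosed volunteer.** The restart rule needs the volunteer to be aware of the mistake. The questionnaire records intake, but the protocol attaches no action to its entries, and coverage of the morning of day 4 is not stated. The four controls can estimate background on the same diet. They cannot reveal one dosed volunteer's lapse.

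**Food lists side by side.** Study Design restricts, among others, rice, maize, polenta, wine and sauce-binders. The restricted column of Figure 2, the list handed to volunteers, names pasta, breads, baking products, breakfast cereals and snacks, and beer as the only beverage; other beverages are permitted. Rice, maize, polenta, wine and sauce-binders are not named. A volunteer could therefore eat or drink a restricted item without knowing it, and the restart rule would not apply.

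**Criterion for a positive blank.** Free share = 100% − 90% = 10%. If the rule means free DON only, it uses about 10/100 = one tenth of the signal carried by free DON plus glucuronides. If it means the sum, nothing is lost. The protocol does not say which, and gives no threshold.

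**Lapses before the blank (illustrative).** The Rationale calls the excretion half-life short without giving a value. Assume first-order excretion with half-life *h* of 2 to 6 hours, *k* = ln 2/*h*, and a blank holding the last 8 hours of urine. For a meal *t* hours before the blank:
- share in blank = exp(−*k*(*t* − 8)) − exp(−*k* *t*)
- carry-over into the outcome window = exp(−*k* *t*)

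| Meal | *t* (h) | Share in blank, total DON | Carry-over |
|---|---|---|---|
| Day 2 dinner | 12 | 23–38% | 1.6–25% |
| Day 2 lunch | 18 | 3–19% | 0.2–12.5% |
| Day 1 meals | 36–47 | at most 2.4% | at most 1.6% |

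Free DON alone would be one tenth of each blank share. The early lapses that the blank hardly shows also add little to the outcome.

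**Size of a lapse inside the window (illustrative).** Assume 100 g of a cereal food at 100 to 500 µg/kg, and a 70 kg volunteer. None of these is in the protocol.
- Dietary DON = 0.1 kg × 100 to 500 µg/kg = 10 to 50 µg.
- Bolus = 70 kg × 1 µg/kg = 70 µg.
- Ratio = 10/70 to 50/70 = 14% to 71%.
- In the DON-3-glucoside period, if the 1 µg/kg is weighed as glucoside, the molar ratio is (10/296)/(70/458) = 22% to (50/296)/(70/458) = 111%.
- One such lapse among 20 dosed volunteers moves the mean by 14/20 = 0.7% to 71/20 = 3.6% of the dose. If the controls come out of the 20, leaving 16, it is 0.9% to 4.5%.

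These ratios compare intakes. A late meal is not fully excreted by the last void, so they are upper guides to the bias.

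**The case against.** A reader might infer that the blank misses most lapses. The protocol does not support that. It gives no half-life value, no detection limit and no lapse rate. About two thirds of the diet hours precede the blank, and under the model above the early lapses that it would barely show carry at most 1.6% into the outcome.

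A reader might also infer that the check discards 90% of the signal. That needs the blank to be judged on free DON alone, which is nowhere stated. The Rationale treats glucuronide analysis as essential, both glucuronides are on the analyte list, and one validated method is used for the samples. Even under a free-DON rule, a missed lapse depends on the detection limit, and the protocol plans to concentrate samples if nothing is detected. What stands is that the criterion is undefined. Analytes and threshold might be set in an analysis plan that is not at hand.

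It is also fair that the protocol admits imperfect control of diet, and that recognised lapses on day 3 already lead to a restart. The remaining exposure is to unrecognised or unreported lapses. The proposed screening can find the former, through recorded foods, but not the latter.

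None of this touches the timing: the blank precedes the whole outcome window.

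**Conclusion.** The point holds in this form. The blank cannot verify the diet during the 24-hour collection, where a lapse adds directly to the measured excretion. Only self-report covers that period in dosed volunteers, and it is weakened by two food lists that do not agree. This conclusion rests on the protocol's own sequence of events and on no assumed figure. The certainty that non-adherence will be detected is therefore not justified.

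Secondarily, the protocol does not say whether a positive blank is judged on free DON or on DON with its glucuronides. The loss to about one tenth of the signal is conditional on the first reading.

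The size of the bias cannot be derived from the protocol. The 14% to 71% applies to a single affected volunteer under assumed portion, contamination and body weight. With one lapse in the group, the effect on the mean would be a few percent of the dose at most. Individual recoveries and profiles are more exposed than the group mean.

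**What to change.** 1. Have the investigators screen each food questionnaire against the Study Design restricted list for the period from bolus to last void, after confirming that the records reach the morning of day 4. Flag affected collections.
2. Report recovery and excretion profiles with and without flagged collections, using the controls' 24-hour molar output as the background estimate.
3. Define a positive blank on the molar sum of DON, its two glucuronides and the other measured forms, and state the threshold. Replace the claim of certain detection with a statement that the blank informs on the period before dosing only.
4. Reconcile the Study Design restrictions with the list given to volunteers.

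The analytes are already measured, and food records and controls are already planned, so items 1 and 2 cost mainly staff time. Item 3 is more than wording: a positive blank currently means repeating the intervention, so a more sensitive criterion may lead to a few more repeats. With only four controls, the background estimate will be imprecise. Lapses that are neither recorded nor reported will remain undetected, and the report should say so.
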